**Table 2 Tab2:** **Numbers of subjects in three batches of the study**

**Batch**	**Group 1**	**Group 2**	**Group 3**	**Total**
1	7	7	7	21
2	8	8	8	24
3	14	14	-	28
Total	29	29	15	73

Group 1: Cognitive behavioral therapy (CBT) with booster sessions group; Group 2: CBT group; Group 3: waiting group.

### Statistical analysis

The main analysis is a two-group ANCOVA of ADHD symptoms, emotional symptomatology, executive function, impulsiveness, self-esteem and life quality at all time points with baseline scores as covariates. To estimate the changes with time in every group, the repeated measures ANOVA will also be used. Furthermore, the neuroimaging data will be analyzed based on a voxel-by-voxel method and the general linear model with a one group by two time points design after pre-processing procedures. The statistics is based on intent-to-treat (ITT) analysis, and the last observation carried forward (LOCF) will be used to address the missing data.

The primary endpoints analysis is ANCOVA with ADHD-RS scores at 12 and 24 weeks separately as dependent variables and baseline ADHD-RS scores as covariates. Other variables that have correlation with ADHD-RS scores and clinical meanings will also be considered for covariates such as gender, age, IQ and education.

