### Objectives/hypotheses

The primary research questions are as follow: (1) Is CBT effective in the treatment of adult ADHD and related problems? and (2) Is the treatment effect of CBT with booster sessions superior to that of CBT only?

There are still other questions: (1) Would booster sessions improve the patients’ satisfaction at evaluation? The subjective evaluation would reflect the acceptability of the treatment, especially in psychotherapy, and these measurements might reflect factors that work other than outcomes of scales or behavioral tests [15,28]. (2) Are there some significant factors that can predict or influence the outcome, including symptom severity, comorbidity, social and economic status, and neuropsychological or neuroimaging biological markers? The role of baseline situations in CBT for adult ADHD remains unclear, and the possible biological markers might benefit finding the “working factors” in CBT [17,29,30]. (3) Would the effects of CBT cause some neuroimaging changes? The neuroimaging methods would provide the biological evidence of treatment and benefit exploring the mechanism of psychotherapy [29]. (4) Finally, considering the limited evidence of long-term effects [17,30], how long the outcomes last would also be evaluated.

The hypothesis of this study is that CBT reduces ADHD symptoms compared to nonintervention, and CBT with booster sessions reduces more ADHD symptoms compared to CBT only.

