## Methods/Design

### Study design

We use a three-armed study design in order to evaluate the effect of CBT on ADHD adults compared with no intervention condition and the effect of 12 weeks CBT with booster sessions versus 12 weeks CBT only. There are three randomized groups, including a CBT with booster sessions group (group 1), a CBT group (group 2) and a waiting group (group 3).

The primary and secondary outcomes will be evaluated at baseline (T1), after 12 weeks of treatment (T2) and after three booster sessions, which is at 24 weeks (T3). Moreover, two ADHD symptom evaluation scales and two emotion evaluation scales will be rated weekly during the 12 weeks of treatment in order to monitor the changes. Patients of the CBT with booster sessions group (group 1) will be followed up at 36 weeks and 48 weeks. Furthermore, the follow-up will be conducted at 24 weeks, 36 weeks and 48 weeks for patients of the CBT group (group 2), and will be at 12 weeks for the waiting group (group 3) patients (Figure 1). Considering the interest of the waiting group patients, on request, we will provide them with 12 weeks of CBT at no charge after the study.

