We summarized the tools and the assessing time points in Table 1. The reasons we used these instruments to measure the efficacy are explained below. Since the ADHD symptoms are the main target of treatment and this manual was specifically designed for ADHD, the measurement of core ADHD symptoms is significant for confirming the effect of CBT. And the level of impulsiveness may manifest the core impairment of ADHD [46]. It was reported that emotional disorders were common for adult ADHD as comorbidities (the lifetime comorbid rates were 19.4% for generalized anxiety disorder and 28% for major depression [47]) and 32% of ADHD adults had emotional dysregulation [48], which makes it important to monitor the change of emotion during the intervention. Furthermore, the latest meta-analysis proved that CBT was effective for depression and anxiety [49], so the emotional results would be positive. The executive function of ADHD adults was reported to be impaired [50], and the BRIEF-A and the CANTAB could test both the ecological and practical aspect [51]. Moreover, the levels of self-esteem and life quality of ADHD adults were also proven to be lower than those of normal controls [52,53]. Additionally, the neuroimaging method as well as the neuropsychological tests could help identify the potential endophenotypic biomarkers that reflect or predict the outcomes of CBT, which would provide a strong evidence of the efficacy of psychotherapy [29]. Given the main consideration of core symptoms and the relatively great change of emotion [12,18,19], these were tested frequently. Furthermore, other aspects were evaluated, as done in previous studies [12-16,27], at three main endpoints, which were before treatment, after CBT and after booster sessions, whereas imaging was conducted at the end of 12 weeks because the efficacy of 12 weeks of CBT on brain functions had not been tested in adult ADHD as had been done in other studies [54,55].

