**Table 1 Tab1:** **Instruments applied at different time points**

**Instruments**	**Baseline**	**Week 2 to 11**	**Week 12**	**Week 24**	**Week 36**	**Week 48**
ADHD-RS	×	×	×	×	×	×
CAARS	×	×	×	×	×	×
SAS	×	×	×	×	×	×
SDS	×	×	×	×	×	×
BRIEF-A	×		×	×		×
CANTAB	×		×			
BIS	×		×	×		×
SES	×		×	×		×
WHOQOL-BRIEF	×		×	×		×
fMRI	×		×			

ADHD-RS, ADHD Rating Scale; CAARS, Conners Adult ADHD Rating Scale Self-report Screening Version; SAS, Self-rating Anxiety Scale; SDS, Self-rating Depression Scale; BRIEF-A, Behavior Rating Inventory of Executive Function-Adult Version; CANTAB, Cambridge Neuropsychological Test Automatic Battery; BIS, Barratt impulsiveness scale; SES, self-esteem scale; WHOQOL-BRIEF, World Health Organization Quality of Life-Brief Version; fMRI, functional magnetic resonance imaging.

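### The fMRI analysis is fixed as a one-group before-after model, which cannot support the causal question and efficacy wording attached to it; the article does not say whether waiting patients are scanned

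*Protocol article*

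**What the plan says.** All places are in the protocol article.

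- **Model.** Statistical analysis states, for neuroimaging, a voxel-by-voxel method with "the general linear model with a one group by two time points design after pre-processing procedures". The same paragraph gives the other outcome domains a between-group analysis: "The main analysis is a two-group ANCOVA of ADHD symptoms, emotional symptomatology, executive function, impulsiveness, self-esteem and life quality". Neuroimaging is not in that list.
- **Question.** Objectives/hypotheses, further question (3), is causal: "Would the effects of CBT cause some neuroimaging changes".
- **Use of the result.** Outcome measures says that imaging and neuropsychological tests could identify biomarkers that reflect or predict the outcome of CBT, "which would provide a strong evidence of the efficacy of psychotherapy". It explains the week-12 scan by noting that "the efficacy of 12 weeks of CBT on brain functions had not been tested in adult ADHD".
- **Timing.** Table 1 marks fMRI at baseline and week 12 and names no arm.
- **Possible control.** Study design says that follow-up "will be at 12 weeks for the waiting group (group 3) patients", so the waiting group is assessed in the week of the second scan. Nothing says whether that assessment includes a scan.

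**The concern.** Imaging is listed among the main secondary endpoints and is meant to show an effect of 12 weeks of CBT on brain function. In a one-group, two-time-point model, the estimated change is the CBT effect plus everything else that differs between the two scans: familiarity with the scanner and task, scanner drift, and the passage of 12 weeks. These parts cannot be separated within one group. A significant map would show that the signal changed in treated patients, not that CBT changed it. The trial randomises a concurrent untreated group up to the same week, which is the comparison that would isolate CBT if those patients are scanned.

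**Working it through.** The article gives no fMRI sample size, variance, effect or alpha, so there is no stated figure to reproduce. The check has two parts.

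**1. The sections side by side**

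| Item | Where | Content |
|---|---|---|
| Question | Objectives/hypotheses, further question (3) | Does CBT cause neuroimaging change? |
| Role | Outcome measures | Evidence of efficacy; also biomarkers of outcome |
| Scans | Table 1 | Baseline and week 12, arms not named |
| Waiting group | Study design | Assessed at week 12, scan not mentioned |
| Model | Statistical analysis | One group, two time points |

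Let the mean change be *c* + *m* in treated patients and *m* in waiting patients, with *c* the CBT effect and *m* all other change. The stated model estimates *c* + *m*. The CBT-minus-waiting difference in change estimates *c*. Question (3) is about *c*.

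At most how many patients could enter that contrast? Table 2 has waiting patients only in batches 1 and 2:

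- CBT: (7 + 8) in group 1 + (7 + 8) in group 2 = 30. Pooling is sound because both groups receive the same treatment to week 12.
- Waiting: 7 + 8 = 15.
- Batch 3 (14 + 14 = 28) has no concurrent waiting patients and is left out of the contrast.

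**2. Illustration of size**

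Assumptions, none from the article: one voxel or region, two-sided 5%, no correction for multiple voxels, normal changes with equal SD in both groups.

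*One-group test when CBT has no effect* (*c* = 0, and *m* equal to *dz* SDs of change). The rejection probability is P(|T| > t(0.975, n − 1)), with T noncentral t on n − 1 degrees of freedom and noncentrality *dz*·√n.

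| n | dz = 0 | 0.2 | 0.3 | 0.5 |
|---|---|---|---|---|
| 15 | 5% | 11% | 19% | 44% |
| 30 (all CBT, batches 1 and 2) | 5% | 19% | 36% | 75% |
| 58 (all CBT, all batches) | 5% | 32% | 61% | 96% |

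The first column shows that the test is sound for the claim that the signal changed. The other columns show how often the same test would be significant although CBT did nothing.

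*Between-group test of change.* When *m* is equal in both arms it cancels, so rejection under *c* = 0 stays at 5%. For a true effect of *d* SDs of change, noncentrality is *d*/√(1/30 + 1/15) = *d*·√10 = 3.16*d* on 43 degrees of freedom:

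| Sizes | d = 0.5 | 0.8 | 1.0 |
|---|---|---|---|
| 30 v 15 | 34% | 70% | 87% |
| 26 v 13 | 30% | 63% | 82% |
| 15 v 15 | 26% | 56% | 75% |

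The second row shows somewhat smaller groups, as drop-out would leave. The third applies if only 15 CBT patients are scanned.

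*Price in power.* If *m* were exactly zero, the one-group test with 30 patients would have 75% power at 0.5 SD, against 34% for the contrast.

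**The case against.** **A reader might infer that the trial holds control scans and ignores them. The article does not show this.** Table 1 restricts no instrument by arm: it marks ADHD-RS, CAARS, SAS and SDS at weeks 24, 36 and 48, although Study design names only week 12 for the waiting group. Its silence on arms therefore does not show who is scanned. The general statement that secondary outcomes are measured at baseline, 12 and 24 weeks is no better evidence, since fMRI has no week-24 scan. The singular group in the stated model would fit a plan to scan treated patients only. This objection stands and makes the remedy conditional.

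**The aim is exploratory.** Question (3) comes after the two primary questions, and its rationale is to explore mechanism. Looking for markers that go with outcome can reasonably start from treated patients. This stands too and lowers the weight of the point. It does not rescue the causal wording or the efficacy claim.

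**The abstract may imply more.** It names fMRI among the secondary endpoints and says that change within each group is analysed in addition, which hints at a between-group analysis. But it gives no such model for fMRI, and Statistical analysis is specific.

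**Some further charges go too far.** Regression to the mean is a lesser threat, because no eligibility criterion selects on brain signal. Medication change is limited at entry by the requirement to be medication naive or stable for at least two months. Nor does the article state a rule that any week-12 change will be credited to CBT; that is a risk of the wording, not a stated plan.

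**Conclusion.** The point holds in a limited form. The one fMRI model stated has no between-group comparison, so it can describe change in treated patients but cannot answer whether CBT caused it or serve as evidence of efficacy. This follows from the article's own text and needs no numerical assumption.

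The size is not known. The illustrated 19% to 75% rejection in 30 patients without any CBT effect rests entirely on the assumed non-CBT change of 0.2 to 0.5 SD and on a single uncorrected test. If that change were zero, there would be no inflation.

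Whether a randomised contrast is possible depends on a fact that the article does not give, namely whether waiting patients are scanned. The endpoint is secondary and exploratory. The ADHD-RS primary analysis, and the two-group ANCOVA of the other listed domains, are untouched.

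**What to change.** First state which groups are scanned. Then:

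- **If waiting patients are scanned:** make the test of question (3) a group-by-time contrast, groups 1 and 2 pooled against waiting, within batches 1 and 2 (at most 30 v 15, fewer if only a subset is scanned). An ANCOVA of the week-12 signal on the baseline signal is an alternative. Report the one-group before-after map as descriptive. The article states no correction for multiple voxels, so whichever one is used should be named for this contrast. The cost is a change of analysis text and lower power than a before-after test, with probably fewer significant voxels.
- **If they are not scanned:** say so, and restate question (3) and the efficacy wording in Outcome measures as describing change within treated patients only. The cost is a weaker claim; no analysis of the existing scans can supply the missing control.

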A review of CBT studies for adult ADHD emphasizes that evidence of long-term outcomes is limited [17]. Through the follow-up of treated patients from our group study, which only used 12 weeks of CBT as described in the manual [18], we found that patients forgot the skills they learned in CBT and had difficulties in applying them into practice in real life. The booster sessions were previously used in behavior therapy to achieve sustaining results, and a review of 30 clinical trials concluded that the booster sessions were useful in maintaining behavioral change [20]. With regard to CBT, according to studies covering depression [21,22], bipolar disorder [23], panic disorder [24] and binge eating disorder [25], providing the booster sessions or the maintaining treatment after the completion of CBT would reduce the recurrence rate and benefit the long-term effect. Furthermore, the latest meta-analyses found that CBT with booster sessions was more effective and had more sustainable outcomes for children with mood or anxiety disorders [26]. To date, three CBT studies for adult ADHD have included periods as booster sessions [13,14,27]; however, the specific effects of this process have not been investigated. In Safren’s study, there is an optional session that contains review and summary of the previous lessons [13]. There were two booster sessions in Weiss’s research at 15 and 20 weeks [14], and 10 booster sessions monthly in Philipsen’s study protocol after 12 weeks of group therapy [27]. None of these above studies considered these periods as separate from the treatment or explored their role in the integrated treatment.

The integration of known CBT interventions for other disorders in adult ADHD remain to be explored [17]. So, we wonder whether the booster sessions could help CBT in fulfilling the skill-teaching and practicing missions, thereby prolonging the efficacy for adults with ADHD. This study is conducted to test whether CBT is effective in the treatment of attention-deficit and emotional, executive and social impairments due to ADHD in a randomized controlled design and to explore the role booster sessions played in the CBT process.

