### Outcome measures

The primary efficacy endpoint is an ADHD Rating Scale (ADHD-RS) [37] score at 12 and 24 weeks. We will measure the different scores between the waiting group (group 3) and the CBT group (group 2) at 12 weeks to prove the effect of 12 weeks CBT on adult ADHD, and between the CBT with booster sessions (group 1) and the CBT group (group 2) at 24 weeks to explore the effect of booster sessions.

The main secondary endpoints will include the following:ADHD symptoms (Conners Adult ADHD Rating Scale Self-report Screening Version [38]) at 2, 3, 4, 5, 6, 7, 8, 9, 10, 11, 36, 48 weeksEmotional symptomatology (Self-rating Anxiety Scale [39], Self-rating Depression Scale [40]) at 2, 3, 4, 5, 6, 7, 8, 9, 10, 11, 12, 24, 36, 48 weeksExecutive function (Behavior Rating Inventory of Executive Function-Adult Version (BRIEF-A) [41], Cambridge Neuropsychological Testing Automated Battery (CANTAB) [42] at 12, 24, 48 weeksImpulsiveness (Barratt impulsiveness scale [43]) at 12, 24, 48 weeksSelf-esteem (self-esteem scale [44]) at 12, 24, 48 weeksLife quality (World Health Organization Quality of Life-Brief Version [45]) at 12, 24, 48 weeksNeuroimaging (Brain Oxygenation Level Dependent Signal) at 12 weeks.

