### Power

It is a noninferiority randomized controlled study, and the primary outcome measure is the mean difference of the ADHD-RS scores between groups. Since there was no relevant study that included booster sessions for adult ADHD, we used the results of a self-controlled preliminary experimental study. At baseline, the score of the ADHD rating scale was 29.80 ± 7.67 (n = 15), after CBT the score was 17.22 ± 7.62 (n = 18), and after booster sessions the score was 10.56 ± 4.98 (n = 16). We assume the drop-out rate is 10%, because the previous studies showed good compliance, and the outpatients are willing to participate [18,19]. So with the power of 80% and alpha of 5% and based on the formula (n = 2[(tα + tβ)*σ/δ]^2, n means number of subjects, tα means t value of alpha, tβ means t value of beta, σ means population standard deviation, δ means deviation), the sample size is about 73 subjects including 15 patients in the waiting group (group 3), 29 in the CBT group (group 2), and 29 in the CBT with booster sessions group (group 1). The numbers of subjects varied in the three groups since the deviations (δ) of ADHD-RS scores after 12 week CBT and after booster sessions were different. Considering the real situation with recruitment, we separated it into three batches, with a total of 21, 24 and 28 subjects for one time (Table 2).

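### LOCF as the only stated missing-data method fixes dropouts at scores the trial expects to change, and can bias both primary contrasts in a direction set by the timing and balance of dropout

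*Protocol article*

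**What the plan says.** The protocol article, Statistical analysis, adopts intention to treat and adds that "the last observation carried forward (LOCF) will be used to address the missing data". The same section defines the primary analysis: "The primary endpoints analysis is ANCOVA with ADHD-RS scores at 12 and 24 weeks separately as dependent variables and baseline ADHD-RS scores as covariates". Outcome measures fixes the two comparisons, the first "between the waiting group (group 3) and the CBT group (group 2) at 12 weeks" and the second "between the CBT with booster sessions (group 1) and the CBT group (group 2) at 24 weeks".

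Three other places bear on whether a constant score is a fair assumption:

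- **Power** gives pilot ADHD-RS means of 29.80 at baseline, 17.22 after CBT and 10.56 after boosters, and assumes 10% dropout. Limitations concedes that this rate may be too low.
- **Background** reports from the group's earlier CBT patients that "patients forgot the skills they learned in CBT and had difficulties in applying them into practice in real life".
- **Study design** says that "two ADHD symptom evaluation scales and two emotion evaluation scales will be rated weekly during the 12 weeks of treatment". Table 1 marks the ADHD-RS at baseline, weeks 2 to 11, 12, 24, 36 and 48. It shows no rating between weeks 12 and 24.

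**The concern.** LOCF is a stated choice here, so the point does not depend on what an unseen SAP may add. It assumes that a patient who leaves would have kept the last recorded score. The trial is built on the opposite expectation: scores improve during CBT, improve further with boosters, and skills slip without them.

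The week-24 question is what happens after week 12. For every patient lost in that interval, LOCF answers that nothing happened. In the week-12 contrast, a CBT patient who leaves early is held at a score that has only partly improved, or not improved at all.

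At stake are the estimates for both primary contrasts and, if the arms lose patients at different rates or times, the type I error of the booster comparison.

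**Working it through.** **Inputs.** The means 29.80, 17.22 and 10.56 and the 10% dropout come from Power; the visit schedule comes from Table 1. The following are assumptions of this check: the waiting group stays at 29.80; group 2 stays at 17.22 after week 12; group 1 reaches 10.56; dropouts would have followed their arm's course. The 20% rate and the unequal splits are also assumed, because the plan does not divide dropout by arm.

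The plan gives no figure for the effect of LOCF. Its sample size of 73 is not an input. No single variant tried of its formula gave both 15 and 29, but nothing here rests on that.

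**Step 1, contrasts without missing data.** Week 12: 29.80 − 17.22 = 12.58. Week 24: 17.22 − 10.56 = 6.66.

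**Step 2, week 24, a share p of each arm lost after week 12.** Each such patient carries the week-12 score, expected to be 17.22. Group 1 becomes (1 − p) × 10.56 + p × 17.22 and group 2 stays at 17.22, so the contrast is (1 − p) × 6.66.

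- p = 0.10: 0.90 × 6.66 = 5.99
- p = 0.20: 0.80 × 6.66 = 5.33

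**Step 3, week 12.** Waiting-group dropouts carry 29.80, which is also their assumed week-12 mean, so only group 2 shifts.

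- Loss straight after baseline, (1 − p) × 12.58: 11.32 at 10% and 10.06 at 20%.
- Loss spread evenly over the treatment weeks with linear improvement, so that about half the gain is carried, (1 − p/2) × 12.58: 11.95 at 10% and 11.32 at 20%. Simulation gave 12.00 and 11.28.

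**Step 4, week 24 with unequal loss.** If the dropouts hold only a baseline score:

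- 15% lost in group 1, 5% in group 2: group 1 = 0.85 × 10.56 + 0.15 × 29.80 = 13.45; group 2 = 0.95 × 17.22 + 0.05 × 29.80 = 17.85; contrast 4.40.
- 5% in group 1, 15% in group 2: group 1 = 0.95 × 10.56 + 0.05 × 29.80 = 11.522; group 2 = 0.85 × 17.22 + 0.15 × 29.80 = 19.107; contrast 7.59.

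Against 6.66, the first is too small and the second too large. If the same unequal losses fall after week 12 instead, the contrasts are 0.85 × 6.66 = 5.66 and 0.95 × 6.66 = 6.33, both too small. Timing and balance together set the direction.

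**Step 5, simulation.** 1,500 trials per scenario, baseline-adjusted ANCOVA, the plan's means and SDs, within-patient correlation 0.6, dropout at random within arm.

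- *Type I error, week 24, nominal 5%, losses of 5% vs 15% in either order:* 7.6% for loss after week 12, 11.1% to 12.5% for loss spread over the treatment weeks, 16.1% to 17.9% for loss straight after baseline. At 5% vs 15% the simulated shifts for the first and last timing, 0.66 and 1.93, match 0.10 × 6.66 = 0.67 and 0.10 × (29.80 − 10.56) = 1.92. So this null has both arms reaching 10.56. If both instead stayed at 17.22, unequal loss after week 12 would cause no shift, and loss straight after baseline would cause 0.10 × 12.58 = 1.26.
- *Type I error, week 12:* 4.0% to 6.2%, so no material inflation.
- *Coverage of the 95% interval:* about 91% to 95% at equal 10% loss, and about 82% in the worst unequal case. The observed-data analysis recovered about 12.6 and 6.7 with about 95% coverage.
- *Standard error at equal 10% loss spread over the treatment weeks (model vs actual spread):* 1.63 vs 1.63 at week 24; 2.01 vs 1.98 at week 12.
- *Power at week 24 under LOCF:* 86% to 97% at equal 10% loss, 67% to 92% at equal 20%, and 60% with 15% vs 5% lost straight after baseline.

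**The case against.** The strongest objection concerns what the true effect is. The figure of 6.66 supposes that group 2 stays flat after week 12, and it credits group 1 dropouts with a booster gain they left before receiving. Under intention to treat, if such patients would simply have kept their week-12 score, 5.99 is the right answer and not a biased one. This stands as a condition on the figure, which is why the verdict states it. It does not rescue the rule: the article gives no such reason for LOCF, and its own account of skills being forgotten speaks against constant scores after treatment.

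The size is also modest at the planned rate. At equal 10% loss the week-24 shift is 6.66 − 5.99 = 0.67 points, and simulated power stays above 80%. That stands. It is no full comfort, because Limitations doubts the 10%. Shrinkage is also not conservative on every reading: Power labels the trial noninferiority although its hypotheses are of superiority.

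Third, the repeated ratings help less than they seem to. None falls between weeks 12 and 24, and the article does not say clearly whether the waiting group is rated weekly. This stands and shapes the fix.

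A reader might infer that LOCF, by treating filled-in values as observed, makes the standard errors too small and the intervals too narrow. The check does not support this as a general claim. Model standard errors matched the actual spread in the scenario shown. At week 24 they were about equal to or above those from observed data (1.45 to 1.86 vs about 1.46 with a true effect). Only at week 12 were they sometimes smaller (1.88 to 1.92 vs about 2.07 with no true effect, at 10% loss). The poor coverage comes mainly from bias.

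**Conclusion.** The concern holds as one of bias. LOCF is the sole stated method for both primary ANCOVAs, and its constancy assumption conflicts with the trial's own expected scores. With equal loss after week 12, and if dropouts would have followed their arm's course, the week-24 contrast falls from 6.66 to 5.99 at 10% and to 5.33 at an assumed 20%. With the waiting group flat at baseline, the week-12 contrast falls from 12.58 to about 11.3 to 12.0 at 10%. Unequal loss can push the week-24 contrast either way and, in the null scenario described, lift its type I error to about 8% to 18%.

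Stronger readings do not follow. That LOCF always pulls the booster effect toward zero is refuted by the 7.59 case. That it favours CBT at week 12 would need natural improvement in the waiting group or worsening among treated dropouts, and the documents give no figure for either. That group 2 will lose more patients, or relapse by some number of points, is likewise unsupported: the Background remark is qualitative and concerns skills, not ADHD-RS scores.

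This should be changed. It is not fatal at the planned dropout rate.

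**What to change.** Replace LOCF in the primary analysis with a likelihood-based repeated-measures model of the ADHD-RS, with group, visit, group-by-visit, baseline and batch. Use weeks 12 and 24 and a few earlier ratings common to the arms, and apply a small-sample correction to the degrees of freedom. Batch belongs in the model because the third batch has no waiting group (Table 2).

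Three details need stating:

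- Group 3 contributes only up to week 12. The week-24 contrast is read from groups 1 and 2.
- Patients with only a baseline score drop out of a model that uses baseline purely as a covariate. To retain them, enter baseline as a response with a mean constrained equal across groups, or use multiple imputation.
- The model still assumes that dropouts resemble similar patients who stay. Add one not-at-random sensitivity analysis that shifts the values of dropouts by a range of deltas. It matters most at week 24, where no rating after week 12 informs the missing score.

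Keep LOCF as a further sensitivity analysis.

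The cost is a change of wording, slightly more programming and a few more covariance parameters in a small trial. No new data are needed, since Table 1 already schedules the ratings. By the Trial status section recruitment was still under way, so on the article's timeline the change could be made before the data are complete.
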